**Figure 1 Fig1:**
[figure not shown]
**Flowchart of study participation.**

### Recruitment

#### Recruitment of primary care clinics

All primary care clinics situated in Newcastle and the surrounding areas of Lake Macquarie, and the lower Hunter (Maitland) were identified via lists held at a regional organization for primary care (Hunter Medicare Local) and via cross-checking with the local white pages electronic phone directory. All practices were invited by telephone to participate. In line with recommendations for conducting research in primary care [33], primary recruitment was conducted by a practicing GP (Chief Investigator [name]) who had clinical credibility with the target group. CI [name] attended a practice meeting at interested clinics to describe the aims of the study and the requirements of participating practices. A second recruitment pool in Inner West Sydney was established through partnership with the Inner West Sydney Medicare Local. The Inner West Sydney Medicare Local held lists of all clinics in the local area, and all GPs were invited to attend a dinner to hear CI [name] describe the study. For GPs that expressed interest in the research study but were unable to attend the GP dinner, a separate face-to-face meeting was scheduled to provide information about the research study. Participating GP clinics in both areas were offered a small fee (AUD$50 for each day) to cover administration expenses for the use of an available room for the research assistant to meet with potential participants.

#### Recruitment of participants

Patients attending appointments at participating practices were advised about the study by GPs, practice nurses, receptionists, and via promotional materials placed in the waiting room and reception area, or a combination of these strategies. The aim was for GPs to identify potentially eligible patients and initiate discussion of the study with them. After discussion with their GP, interested patients were asked to book an appointment on one of the pre-determined recruitment days to speak to a research assistant about the study. There has been a blurring in previous trials between ‘GP referral’ and ‘recruitment from the primary care setting’. The first maximizes the influence of the doctor-patient relationship and inherently involves the clinician in patient care, whilst the second utilizes the primary care setting to identify potentially eligible patients, and may or may not involve the treating clinician (e.g., having a research assistant recruit patients from the clinic waiting room). To maintain the method most closely resembling real world practice and to ensure a genuine GP referral pathway, situating a research assistant in the waiting room for recruitment was not employed in the current trial. This pragmatic approach needed to be balanced with limiting the amount of time required by GPs or other practice staff to undertake patient screening (that related to the research trial and would not be necessary in usual practice for a referral scheme) [33]. For this reason, following identification and referral of the potentially eligible patient, a study-specific research assistant undertook all study screening and consent-related activities during a scheduled appointment at the practice rooms.

### Eligibility and screening

During the scheduled appointment, the research assistant explained the study and obtained informed consent from patients who met the following eligibility criteria: 18 years of age or older, with regular access to a telephone, able to complete the study measures and interventions in English, plan to live within the defined geographic recruitment area for the following 12 months and willing to undergo screening. Patients needed to be able to safely participate in either of the interventions (face-to-face only, or face-to-face and telephone).

A two-stage screening process was used. Firstly, during the scheduled appointment with the research assistant, consenting patients were screened using the Timed Up and Go three metre test [34]. Patients who took longer than 19.9 seconds [34] to rise from a chair, walk three metres, turn around, and walk back were excluded as they were considered too frail or disabled to begin an unsupervised physical activity program without appropriate rehabilitation. The second stage of screening occurred after the appointment and required the patient to wear a pedometer and record on a log sheet their step count for seven days. Patients posted back the completed log sheet and, after assessment by the research manager, were excluded if they achieved more than an average of 7000 steps per day [35]. This was a more stringent eligibility measurement of current PA than the commonly utilized self-reported method of screening but was deemed necessary to: a) ensure sample were insufficiently active at baseline and therefore avoid potential ceiling effect; and b) exclude potential participants who were very active and may have been interested in accessing specialist exercise advice to enhance performance.

### Randomization and blinding

Random allocation of eligible participants was conducted in two stages, and in order to offer participants a service that was geographically accessible they were asked to indicate the suburbs where they would prefer to see an EP. First, eligible patients were randomly assigned in a 1:2 ratio to the usual care group or to the intervention group using a randomized block design stratified by participant gender with block sizes of 6. Second, those allocated to the intervention group were randomly assigned in a 1:1 ratio to face-to-face only or face-to-face and telephone counseling using a randomized block design stratified by participant gender and the suburb location of the EP, using block sizes of 6. The randomization process occurred on computer at a centralized location by an independent statistician. Participants were notified of group allocation by letter. Central randomization allowed concealment of allocation from research assistants and GPs until group assignment had occurred. Blinding of participants and EPs was not feasible. Contamination was minimized as the intervention was not delivered at the primary care site and follow-up data collection occurred by mail, with patient-reported survey and pedometer-assessed step counts, so was not influenced by study team members. The data analyst was blinded to group allocation, as surveys were de-identified and did not contain study group information.

### Interventions

Physical activity behavior change counseling was guided by Bandura’s Social Cognitive Theory (SCT) [36]. The constructs operationalized as part of the intervention included: self-efficacy, outcome expectations, social support, perceived physical environment, attitudes, confidence to change behavior, goals and intentions.

The physical activity behavior change counseling was delivered by accredited EPs in private practice. All accredited EPs working within the geographic areas were invited to participate in the study. EPs provided the following information: a curriculum vitae, two referees, current professional indemnity and public liability insurance certification, and proof of professional membership of ESSA. EPs attended a five hour study-specific training session conducted by members of the research team with expertise in theory-driven behavior change and communication skills. The training comprised a mix of oral presentations, written information, role plays, feedback, and small group discussion, based on effective evidence-based physician training strategies [37]. The content of the training session covered the importance of behavior change theory (especially SCT) and how to operationalize SCT constructs using a patient-centred behavior change counseling approach.

#### Group 1: referral for face-to-face physical activity counseling

Participants randomized to Group 1 attended five face-to-face consultations with an EP over the 13-week intervention period (13 weeks from date of randomization). The initial consultation was approximately 60 minutes, and each follow-up appointment was approximately 30 minutes in duration. The EP consultations were at no cost to participants, and EPs were reimbursed by the research team at a rate of AUD$90 per initial consultation and AUD$55 per follow-up consultation. Consultations occurred at the EPs private practice. The initial consultation comprised an assessment of the participant’s ability to safely undertake physical activity, and the application of behavior change strategies to enhance participation in physical activity, such as goal setting, the identification of barriers to physical activity and collaborative problem-solving to identify strategies to overcome personal barriers to physical activity. At follow-up visits, progress against goals was assessed, new goals set, and any challenges discussed using the same collaborative problem-solving approach. All consultations were patient-centred and tailored to the participant’s physical activity preferences, capability, medical limitations (if present) and personal barriers. Discussion of cognitive and behavioral strategies, derived from SCT, occurred as appropriate to each person’s motivational readiness to change. Beyond the training in patient-centred counseling and behavior change strategies, there was no other attempt to standardize the intervention and its delivery across participants, EPs, or geographic location.

#### Group 2: referral for face-to-face and telephone physical activity counseling

Participants randomized to Group 2 attended one face-to-face consultation (60 minutes) with an EP and participated in four telephone counseling sessions with the same EP over the 13-week intervention period. The telephone calls were expected to take 30 minutes. The aims and content of the initial and subsequent consultations were the same as for Group 1.

If an EP assessed during the initial face-to-face consultation that the patient in either Group 1 or Group 2 had a complex medical issue that would prevent them from being able to safely undertake increased exercise without appropriate supervision, then participants were deemed ineligible, and were excluded from the intervention and follow-ups.

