**Methods:**

This three arm pragmatic randomized trial will involve the recruitment of 261 patients from primary care clinics in metropolitan and regional areas of New South Wales, Australia. Insufficiently active (less than 7000 steps/day) consenting adult patients will be randomly assigned to: 1) five face-to-face counseling sessions, 2) one face-to-face counseling session followed by four telephone calls, or 3) a generic mailed physical activity brochure (usual care). The interventions will operationalize social cognitive theory via a behavior change counseling framework. Participants will complete a survey and seven days of pedometry at baseline, and at three and 12 months post-randomization. The primary analyses will be based on intention-to-treat principles and will compare: (i) mean change in average daily step counts between baseline and 12 months for the combined intervention group (Group 1: face-to-face, and Group 2: telephone) and usual care (Group 3); (ii) step counts at 3 months post-randomization. Secondary outcomes include: self-reported physical activity, sedentary behavior, quality of life, and depression.

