#### Group 3: usual care

Group 3 received usual care from their GP and were mailed a generic health promotion brochure promoting physical activity and outlining the National Physical Activity Guidelines for Australians [38].

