### Statistical analyses

Baseline data will be summarized as the number of observations, means, standard deviations, medians, minimums and maximums where the data are continuous and as number of observations and frequencies where the data are categorical. The data will be presented separately by treatment group.

The primary endpoint (mean change in daily step counts from baseline to 12 months) will be analyzed using a constrained linear mixed model approach [61], where the outcome in the model is the mean number of steps per day at each time point, but the baseline mean responses for the treatment groups are assumed equal. This approach has been shown to be robust when missing data depend on baseline values [62]. Predictor variables in the model will include fixed effects for group (usual care as reference and group 1: face-to-face, group 2: telephone), time (baseline as reference, 3 months and 12 months) and the interaction between group and time. A subject level random intercept will be included in the model to allow for correlations arising from repeated measures. There may be some variation to this model after checking its underlying assumptions of multivariate normality, linearity and equal variance and clustering. The primary comparison will be between the combined intervention groups (group 1: face-to-face and group 2: telephone) and usual care. A secondary analysis will examine the difference in step counts at 3 months, and if significant differences are found in the primary analysis, will also explore if there are differences between treatment groups (face-to-face and telephone). Sub group analyses will be conducted by sex, BMI category and diagnosed chronic disease versus none. Sensitivity analyses will explore the impact of individual EP, GP clinic, and after removing the steps imputed from self-reported physical activity. The analysis will be conducted on an intention-to-treat basis with alternative methods of accounting for missing data: multiple imputation, and pattern mixture modelling [63].

Process evaluation will be assessed by calculating adherence with intervention (mean number of sessions completed, average time of intervention delivery for face-to-face and telephone counseling sessions). Intervention fidelity will be assessed by coding of EP checklists.

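### Exercise physiologists' post-randomization exclusions stop follow-up in the two intervention arms only, which conflicts with intention-to-treat and could bias the primary comparison

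*Protocol article*

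**What the plan says.** The rule stands at the end of the protocol article's section on Group 2. Its trigger is "If an EP assessed during the initial face-to-face consultation that the patient in either Group 1 or Group 2 had a complex medical issue"; the issue has to be one ruling out safe, unsupervised exercise. The stated consequence is "then participants were deemed ineligible, and were excluded from the intervention and follow-ups".

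Four other places fix the context:

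- The Group 1 section describes "five face-to-face consultations with an EP over the 13-week intervention period (13 weeks from date of randomization", so the intervention period, including the first consultation, runs from randomization.
- Randomization and blinding says "Blinding of participants and EPs was not feasible".
- For usual care, "Group 3 received usual care from their GP and were mailed a generic health promotion brochure promoting physical activity". No EP assessment is described for this arm.
- Eligibility and screening sets a safety condition for everyone before randomization ("Patients needed to be able to safely participate in either of the interventions") and adds the Timed Up and Go test.

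On analysis, the abstract states "The primary analyses will be based on intention-to-treat principles" and the Statistical analyses section states "The analysis will be conducted on an intention-to-treat basis", with multiple imputation and pattern mixture modelling named for missing data. The article does not say how the excluded participants enter the analysis.

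**The concern.** A check that can end follow-up is made after allocation, by a clinician who knows the allocation, and only in the arms on one side of the primary comparison. A usual-care participant with the same medical issue is never assessed this way and is followed to 12 months. The groups with outcome data are then no longer the groups that were randomized.

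Excluding ineligible patients after randomization can be defended when the same check is made in every arm without knowledge of allocation. Neither condition is met here.

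The combined intervention versus usual care comparison of 12-month step change is at stake. The people removed are those judged unable to increase exercise safely without supervision, and they receive no further counseling. They would probably have gained least, so leaving them out would tend to raise the intervention mean. The planned subgroup analysis by diagnosed chronic disease may be affected as well.

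**Working it through.** **The plan's own figures.** The Sample size section gives a difference of 1000 steps/day, SD 2500, 90% power, 5% significance, 79 per group, and 87 per group (261 in total) after 10% attrition. Take two arms combined against one (ratio 2:1) and the normal approximation.

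- Formula: n in usual care = (z for alpha + z for power)² × 2500² × (1 + 1/2) / 1000².
- One-sided 5%: (1.645 + 1.282)² × 9.375 = 80.3, so 81. Power at 79 versus 158 is 89.6%, close to the stated 90%.
- Two-sided 5%: (1.960 + 1.282)² × 9.375 = 98.5, so 99. Power at 79 versus 158 is 82.7%.
- Inflation: 79 × 1.10 = 86.9, so 87 per group and 261 in total.

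Sidedness is not stated, and the present point does not depend on it. These figures serve only to set the scale. The standard error of the primary contrast is 2500 × √(1/79 + 1/158) = about 344 steps/day.

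**Bias formula.** Let f be the excluded share of the intervention arms. Let D be the mean 12-month change in retained participants minus the mean change that the excluded would have shown. The full-arm mean is (1 − f) × retained mean + f × excluded mean, so

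retained mean − full-arm mean = f × D.

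D has to be a difference in change, because the primary endpoint is change from baseline. A difference in 12-month level would partly reflect lower starting values.

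**Values.** The article gives neither f nor D, so both are assumed. The intervention arms hold 2 × 87 = 174 people.

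| f (people of 174) | D = 500 | D = 1000 | D = 2000 |
|---|---|---|---|
| 2% (about 3) | 10 | 20 | 40 |
| 5% (about 9) | 25 | 50 | 100 |
| 10% (about 17) | 50 | 100 | 200 |

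Entries are steps/day. Against the 1000-step target they run from 1% to 20%. Against the standard error they run from 10/344 = 0.03 to 200/344 = 0.58. A negative D reverses the sign.

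**Effect on the test.** Suppose there is no true effect, D is wholly prognostic, and the excluded are simply left out. In the worst cell the standard error becomes 2500 × √(1/79 + 1/142.2) = about 351, and 200/351 = 0.57. The two-sided error is then Φ(0.57 − 1.96) + Φ(−0.57 − 1.96) = about 8.8%. Over the whole grid it runs from 5.0% to 8.8%.

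**What the planned models can recover.** Baseline step counts exist for everyone randomized, since they are part of screening, and baseline is an outcome in the constrained mixed model. An excluded person can therefore contribute a baseline record, and any part of D explained by baseline steps is then absorbed. The article describes the model as robust when missingness depends on baseline values. Arm is in the model, but the EP's medical judgement is not, beyond what baseline steps reflect. A missing-at-random model would also predict these people's outcomes from same-arm participants who went on to receive counseling.

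**The case against.** The strongest reply is that the rule removes people from intervention and follow-up but does not expressly remove them from the analysis. They can enter the mixed model on baseline data. Multiple imputation and pattern mixture modelling are already named, and the latter can represent outcomes that are not missing at random. Definition of the analysis set may also sit in a statistical analysis plan that is not shown. This stands in part. A reader might infer that missing-data methods cannot repair the problem at all, and the article does not support that. What remains is that declaring someone ineligible puts their place in the analysis set in doubt, and that no later document can supply outcomes that were never collected.

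The second reply is that the effect may be small. GP identification, the safe-participation criterion and the Timed Up and Go test all come before randomization, so few may be excluded. This stands, and it is why the table starts at 2% and 500 steps.

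Three further inferences are tempting but unsupported:

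- That the bias certainly favours the intervention. No section reports how excluded participants would have changed, so the direction is a reasoned inference.
- That these losses come on top of the 10% attrition allowance. The Sample size section does not say what the 10% includes.
- That falls and injuries go unrecorded in the trial's highest-risk participants. No one is ranked by risk, and the EP checklist covers the first consultation. Only the later survey reports are lost.

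**Conclusion.** The concern holds as a conflict between an express rule and the stated analysis principle. Outcome data are lost by design in Groups 1 and 2 only, on an unblinded judgement with no usual-care counterpart. The promised intention-to-treat analysis therefore cannot be carried out in full, and the passages must be reconciled.

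The resulting bias is possible and probably favours the intervention. Its size is not known. The range of about 10 to 200 steps/day rests wholly on the assumed f and D, and it applies before any recovery through baseline data and missing-data models. That recovery requires the excluded participants to stay in the analysis set. The case for acting rests on the one-sided exclusion itself, not on a demonstrated large bias.

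**What to change.** Leave the EP's decision about the intervention exactly as it is, and separate it from follow-up and analysis status.

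- In the Group 2 section, delete the words that declare these participants ineligible and those that extend the exclusion to follow-ups.
- Keep sending them the mailed 3- and 12-month survey and pedometer.
- Analyse them in their randomized arm.

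The methods are written in the past tense and the analyses in the future tense, so some follow-up may already have been missed. In that case:

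- Keep these participants' baseline data in the primary mixed model.
- Treat their outcomes as missing in the multiple-imputation and pattern-mixture analyses, with a not-missing-at-random scenario for this group.
- Report the number excluded per arm.

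The cost is a change of wording, some extra mailings where follow-up is still open (about 3 to 17 people under the assumed shares), and possibly a slightly smaller effect estimate.

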#### Group 3: usual care

Group 3 received usual care from their GP and were mailed a generic health promotion brochure promoting physical activity and outlining the National Physical Activity Guidelines for Australians [38].

### Intervention fidelity and process evaluation

During each EP consultation, the EP completed a checklist of topics covered during the consultation. Consultation checklists were returned to researchers with invoices for each of the consultations. The checklists were used to assess: the number of sessions completed with each participant, and the duration of each consultation, and any falls or injuries. The checklists also provided information on whether any of the following SCT strategies were discussed during each consultation: confidence to change behavior, goal setting, physical activity planning, goal review and monitoring, overcoming barriers, sources of social support, and sources of environmental support.

### Outcomes

Participants completed seven days of pedometry and completed a pen and paper survey at three and 12 months post-randomization.

